#### Practical Training:

Three days of practical training for nurses (6 hours per day): Management of ambulatory monitoring study and interpretation of the records. Basic training in more complex studies.

Three days of practical training for physicians (6 hours per day): Indication and interpretation of ambulatory monitoring studies. Outpatient clinical management.

#### 2.- Design and Validation Time:

All patients eligible for inclusion in the study will perform the two models of validation (in the Primary Care center or in the Sleep Unit), as shown below (Stages 1 and 2):

[figure not shown]

Ambulatory Monitoring Study (AMS):

The study will be performed in the patient's home with a Screen & GO device (BITMED, SibelGroup, Spain). The Primary Care nurse will record the anthropometric variables on the day before the test, will train the patient in the use of the device and will program it according to the usual sleep rhythm of the patient. To ensure the correct management of the equipment, a sheet with some instructions will be given to the patient.

The device will be returned to the Primary Care center the following morning. A brief questionnaire about the quality of sleep on the night of the study will be collected, estimating the start and end of the test. The nurse will be responsible for analyzing the quality of the study and will remove periods of poor signal but will not analyze the respiratory events manually: the recording time will be defined as the time passed from 15 minutes after sleep onset (according to previous questionnaire) to 10 minutes before completion. The minimum valid record-time will be 5 hours.

The analysis of the study will be done automatically by the device software. The following variables will be collected: mean SO2, ID4%, ID3%; CT90% and AHI.

The study could be repeated (only once) if a high percentage of poor signal acquisition is detected or if the patient reports poor quality of sleep during the night of the study.

To complete the assessment, a standard sleep study by RP / PSG will be performed, allowing for the final validation of the process.

The final treatment decision will always be made by the physician involved in the project, either in the Primary Care centre or in the Sleep Unit.

RP / conventional PSG: in every case, an overnight sleep study will be done in the Sleep Unit. Conventional PSG must include at least 6 channels: electroencephalography (EEG), electrooculography (EOG), mental electromyography (EMG), hemoglobin oxygen saturation detected by oximetry, oro-nasal airflow by thermistor and nasal-cannula, thoraco-abdominal movements by inductance plethysmography, electrocardiography (ECG), anterior-tibial electromyography and body position. RP will include every channel except EEG, EOG, EMG and ECG. The staging of sleep and respiratory events will be analyzed by the technician of the Sleep Unit, who will be blind to the results of the study at Primary Care level. The sleep study will be classified according to published guidelines (AASM 2007, SEPAR Manual procedures). The minimum recording time should be 6 hours and the minimum total sleep time, 3 hours.

The following data will be collected: Apnea-hypopnea index (AHI), obstructive apnea index, hypopnea index, central apnea index, mixed apnea index, sleep efficiency (total sleep

time/record time), percentage of time in phases NREM1, NREM2, NREM3 and REM, initial saturation, mean saturation (SO2), minimum saturation and cumulative time percentage with saturation lower than 90% (CT90%).

#### Data management and analysis

The main objective of this study is to obtain a sufficiently accurate calculation of the area under the curve (AUC) of the Receiver Operating Characteristics (ROC) curve. The expected sensitivity value is high, close to 90%. With this number of cases the accuracy of the AUC will not be less than 10%. In all cases, the interval confidence of calculated rates is assumed to be 95%.

A descriptive analysis will be performed using means, medians, confidence intervals, interquartile ranges for quantitative variables and table of frequencies for qualitative variables. In qualitative variables, the Chi-square test or Fisher exact test will be used for bivariate analysis. In the case of quantitative variables, the T-test or Mann-Whitney U test will be performed according to normal distribution.

Finally, logistic regression will be used to find the best clinical prediction model. Variables showing clinical significance in the bivariate analysis and those considered clinically relevant will be included. A goodness-of-fit test (Hosmer Lemeshow test) will be performed to validate the resulting model. The AUC of the ROC will be used to calibrate the model.

In all cases, the significance level will be, as usual, 5% ( $\alpha = 0.05$ ), bilateral approach.

We will use IBM-SPSS (V. 21.0) software to perform the analysis.

In the analysis of costs we will consider the direct costs of all the tests (ambulatory monitoring study, polygraphy or polysomnography), staffing costs, the amortization of the devices, the transfer of the patients and the number of visits. We will also take into account the false-positive and negative diagnosis (*Pietzoch JB et al. An integrated Health-Economic Analysis of Diagnostic and Therapeutic strategies in the treatment of moderate to severe obstructive sleep apnea. Sleep 2011;34: 695-709*).

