## **General and specific objectives**

### General objective:

The main purpose of this project is to develop and validate a work-model for Primary Care for identifying patients with OSA, based on clinical variables and an ambulatory monitoring study.

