### Outcome Measures

- Primary outcome: apnea-hypopnea index (AHI) obtained in Sleep Unit by PSG/RP study.
- Secondary outcomes:

Anthropometric and socio-demographic data: age, sex, weight, height, body mass index (BMI) and waist circumference.

Evaluation of medical history and cardiovascular risk factors: hypertension, diabetes, dyslipidemia, smoking, alcoholism, metabolic syndrome, heart disease (ischemic heart disease, arrhythmia, heart failure), cerebro-vascular disease (transient ischemic attack, ischemic or hemorrhagic) and peripheral vascular disease. Drug treatment.

Medical records focussed on Respiratory Sleep Disorders: specific clinical questionnaire on symptoms suggestive of OSA. Berlin-questionnaire in Spanish version. (Chest 2003;124:1406-1414).

Lung function tests: spirometry according to SEPAR recommendations. (Arch Bronconeumol 2013; 49: 388-401).

Self-perceived sleepiness analyzed by Epworth scale (MW Johns, Sleep 1991; 14: 540; validation in Castilian: Med Clin Ferrer M 1999.113: 250-255.).

Respiratory Polygraphy (RP) / Conventional Polysomnography (PSG):

Apnea-hypopnea index (IAH), obstructive apnea index, hypopnea index, central apnea index, mixed apnea index, sleep efficiency (total sleep time/recording time), percentage of time of phases NREM1, NREM2, NREM3 and REM, initial saturation, mean saturation (SO2), minimum saturation and cumulative time percentage with saturation lower than 90% (CT90%).

Ambulatory monitoring study (AMS): AHI, mean saturation, 4% desaturation index (ID4%), 3% desaturation index (ID3%) and CT90%.

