### Sample size

The sample size has been calculated considering a minimum prevalence of 25% of OSA in the population attending Primary Care Medicine. Assuming 15% of losses to follow-up, an error of 5% and a power of 90%, a total sample of 198 patients was estimated as necessary to achieve a sensitivity of 90%.

According to the methodology proposed by Chai-Coetzer et al. (Thorax 2011; 66: 213-219), the screening study will be carried out taking into account clinical probability based on the Berlin Questionnaire (Netzer NC. Chest 2003; 124:1406-14). The study will be carried out in all patients with a high probability of OSA but in only 1 of 3 patients with a low probability. Therefore, a minimum of 396 valid questionnaires must be completed.

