## Limitations

- Limitations of RP: sleep time is not equivalent to study time and this can underestimate the values. To avoid this, we will take into account the quality of sleep provided by the patient. Thus, this aspect will not significantly limit the main objective: to differentiate patients with severe disease or mild disorders.
- Acceptance rate of participation: In a previous study with similar characteristics, the acceptance rate of participation was 40% of the survey respondents. Considering the large population usually attended at Primary Care centers in the urban area of Barcelona, this is not an expected limitation for reaching sample size. We must take into account that patients accepting their inclusion in the study could be those with greater comorbidity. This could give rise to a bias in the sample.

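### The protocol's sections disagree on what the study primarily estimates, and accuracy figures chosen and assessed in the same patients will be optimistic

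*Protocol*

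**What the plan says.** Five places in the protocol bear on what is primary.

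- Under General objective, the aim is given as "The main purpose of this project is to develop and validate a work-model for Primary Care for identifying patients with OSA". That model is to combine results from ambulatory monitoring (the AMS) with clinical data.
- Outcome Measures has this entry: "Primary outcome: apnea-hypopnea index (AHI) obtained in Sleep Unit by PSG/RP study".
- Sample size states that "a total sample of 198 patients was estimated as necessary to achieve a sensitivity of 90" per cent.
- The section Data management and analysis puts it differently: "The main objective of this study is to obtain a sufficiently accurate calculation of the area under the curve (AUC"), here for a ROC analysis. Its next sentence expects a sensitivity near 90%.
- Limitations speaks of "the main objective: to differentiate patients with severe disease or mild disorders".

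The index test has several candidates. For the AMS, the Design and Validation Time section says "The following variables will be collected: mean SO 2 , ID4%, ID3%; CT90% and AHI", with none of the five put first. The clinical-plus-AMS logistic model is a further candidate. Specific objectives lists the validity of the device and the creation of the model as separate items and does not rank them.

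Model variables enter through the bivariate analysis or clinical relevance. The model is to be validated by a Hosmer-Lemeshow test, and the AUC is said to calibrate it. AHI values above 15 and above 30 appear only in the Background, in relation to cardiovascular risk.

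**The concern.** An accuracy study needs four things fixed together: the index test, the reference standard with the value that defines a case, the accuracy measure, and, for sensitivity and specificity, the cut-off. The protocol names measures in different sections and does not join them to a test or a case definition. The Sleep Unit AHI is the reference against which accuracy is judged, so calling it the primary outcome does not say what is estimated. A main objective of separating severe from mild disease is a different classification from separating OSA from no OSA.

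Two things are at stake. First, the headline figure could come from any of several indices, or from the model, at a cut-off found in the same patients, and such figures are optimistic on average. Second, sensitivity without its specificity does not speak to the purpose given under Rationale, which is to spare Sleep Units many referrals.

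**Working it through.** **1. Reproducing the sample size.** Inputs from Sample size: "considering a minimum prevalence of 25% of OSA in the population attending Primary Care Medicine", 15% losses, 5% error, 90% power, sensitivity 0.90. The two-sided approach comes from Data management and analysis. No null sensitivity is given; 0.70 is assumed here.

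n(cases) = [1.96·√(0.70·0.30) + 1.2816·√(0.90·0.10)]² / (0.90 − 0.70)² = (0.8982 + 0.3845)² / 0.04 = 41.1, so 42.

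42 / 0.25 = 168, and 168 / 0.85 = 197.6, so 198.

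This matches exactly, but not uniquely. A precision of ±9 points gives 43 cases and 172 patients, and 172 × 1.15 = 197.8 also rounds to 198. With the same test formula, a null of 0.65 gives 132 and a null of 0.75 gives 320. So 198 is attainable, but the text does not show which test, cut-off or null it serves.

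**2. Precision of the AUC.** With m = 42 cases and n = 126 non-cases, Hanley-McNeil gives SE² = [A(1−A) + (m−1)(A/(2−A) − A²) + (n−1)(2A²/(1+A) − A²)] / (mn). At A = 0.90 this is (0.090 + 0.335 + 5.329) / 5292 = 0.00109, so the 95% half-width is 1.96 × 0.0330 = 0.065. At A = 0.80 it is 0.086 and at A = 0.70 it is 0.097. The protocol's 10% precision statement is consistent with these.

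**3. What 90% sensitivity implies alone.** For a binormal, equal-variance index, d = √2·Φ⁻¹(AUC), and specificity at 90% sensitivity is Φ(d − 1.2816).

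| AUC | d | Specificity at 90% sensitivity |
|---|---|---|
| 0.70 | 0.742 | 0.29 |
| 0.80 | 1.190 | 0.46 |
| 0.90 | 1.812 | 0.70 |

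The same sensitivity goes with very different false-positive rates.

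**4. Optimism from choosing and assessing in the same patients.** Assumptions, none of them from the protocol: 42 cases and 126 non-cases, five equally good binormal indices with pairwise correlation ρ, and a cut-off at the Youden point of the same data (1,500 simulated studies per setting). Sensitivities are apparent / true at the chosen cut-off.

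| True AUC | ρ | Mean AUC, one named index | Mean AUC, best of five | Sensitivity, one named index | Sensitivity, best of five |
|---|---|---|---|---|---|
| 0.80 | 0.5 | 0.799 | 0.832 | 0.761 / 0.707 | 0.798 / 0.702 |
| 0.80 | 0.7 | 0.800 | 0.827 | 0.761 / 0.704 | 0.791 / 0.701 |
| 0.80 | 0.9 | 0.801 | 0.817 | 0.762 / 0.704 | 0.779 / 0.700 |
| 0.90 | 0.5 | 0.901 | 0.924 | 0.848 / 0.799 | 0.877 / 0.792 |
| 0.90 | 0.9 | 0.900 | 0.911 | 0.847 / 0.798 | 0.864 / 0.799 |

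At a true AUC of 0.80, 8,000 runs with ρ from 0.9 to 0.3 put the best-of-five mean at 0.815 to 0.838. The excess in AUC is thus about 0.015 to 0.04. The excess in sensitivity at that AUC is 5 to 6 points when only the cut-off is chosen, and 8 to 10 points when the index is chosen too.

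**5. The model.** Selecting variables on the data and computing the AUC on the same patients biases it in the same direction. A Hosmer-Lemeshow test compares predicted with observed frequencies in those patients, so it neither detects nor corrects this. No size is claimed, because the protocol does not fix the number or strength of the candidate variables.

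**The case against.** The sections can partly be read together: the Sleep Unit AHI as the thing predicted, the AUC as the accuracy measure, and 90% sensitivity as an expected point on the curve. Only Outcome Measures uses the word primary, and in Sample size the sensitivity is a sizing input. The general objective is the combined model, and the analysis section links the AUC to the model, so the text leans that way. Much of this stands. It does not remove the different main objective in Limitations, the missing link between the 90% and any test, or the missing case definition.

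A reader might infer that the best of several indices could decide the trial, that the 90% target cannot fail, or that a family-wise error rate is inflated. The protocol does not support these readings: it states an estimation aim and has no formal success rule. Nor does it say that the best AMS index will be the headline result or that a Youden cut-off will be used, so overstatement is conditional.

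The simulated sizes also have limits. Five equally good indices is an unfavourable case, and the optimism shrinks if one is clearly better. The 42/126 split applies 25% prevalence to the tested patients, yet Sample size tests every patient with a high Berlin probability and one in three of the rest, so the tested case mix should differ. That was not varied.

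The statistical analysis plan is not at hand and may settle cut-offs and rankings. The figure under Design and Validation Time was not available for this review and might carry a cut-off. Neither makes the protocol's own sections agree.

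**Conclusion.** The concern holds as an inconsistency within the protocol. Outcome Measures, Sample size, Data management and analysis, and Limitations do not agree on the primary quantity. The readable text does not tie the AUC or the sensitivity to one index test, one case-defining AHI, or a cut-off with its specificity.

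The consequence is conditional: whatever is selected and assessed in the same patients will look too good on average. Under the illustrative assumptions with a true AUC of 0.80, that is about 0.015 to 0.04 in AUC for the best of five indices and about 5 to 10 points in sensitivity for a data-chosen cut-off. The AUC of one pre-named index is unbiased, and choosing a cut-off affects sensitivity and specificity but not the AUC.

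A reader might also conclude that 198 patients is wrong. That is not shown: the figure reproduces under an unstated null of 0.70. The data would stay usable, and the change should be made before the reference results are linked.

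**What to change.** Use one hierarchy in Outcome Measures, Sample size, Data management and analysis, and Limitations.

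- **Primary measure:** the AUC, with 95% CI, of the clinical-plus-AMS model, as the general objective implies, against a Sleep Unit AHI case definition that the sponsor states once and uses throughout. Call the Sleep Unit AHI the reference standard.
- **First secondary:** the AUC of one AMS output that the sponsor names in advance. Label the other AMS outputs exploratory.
- **Sensitivity and specificity:** report them as a pair, at a cut-off fixed before the reference results are linked.
- **Data-driven choices:** where variables, index or cut-off are chosen on the data, repeat every selection step inside each bootstrap sample. Report the optimism-corrected AUC as well as the corrected sensitivity/specificity pair.
- **Sample size:** tie the 90% sensitivity to that test and cut-off, with the accompanying specificity, and state the null or precision behind 198.

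The cost is wording in four sections and a bootstrap in the analysis, with no more patients or data. The downside is that reported accuracy will be somewhat lower and the remaining AMS indices become exploratory.

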## **Rationale**

The purpose of this project is to assess the efficacy of a sequential screening model in Primary Care centers for detecting and classifying patients with OSA according to severity. The clinical model used will, like recent studies published in the literature, be based on a set of clinical variables and the data obtained by a simplified monitoring device.

To achieve this, we have at our disposal three Sleep Units, attending an urban population of more than one million inhabitants and six Primary Care groups with different administrative and operational structures.

If the results are as expected, this screening model will prove to be a simple tool for screening for OSA at Primary Care level, thereby making it possible to avoid the referral of a large number of patients to Sleep Units. After a first analysis at Primary Care level, PCPs would be able to rule out OSA and, moreover, prioritize patients with severe disease.

Finally, we believe that the availability of this screening-model will have a positive effect on the impact of this disease and its process costs.

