### Specific objectives:

- To establish the validity of an ambulatory monitoring device for identifying patients with OSA and to compare it with the RP / PSG performed at the Sleep Unit.
- To create a screening model for the detection of OSA.
- To analyze the validity of the treatment decision (CPAP vs. no CPAP) made by the PCPs, by using the ambulatory monitoring study, in relation to the decision made by the specialist Sleep Unit.
- To make an analysis of costs, including the cost-effectiveness of an outpatient strategy vs. a strategy including assessment at the Sleep Unit.

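### The AUC alone cannot show whether the AMS AHI can be read at face value for severity; a within-patient agreement analysis against RP/PSG should be added

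*Protocol*

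**What the plan says.** The first specific objective is "To establish the validity of an ambulatory monitoring device for identifying patients with OSA and to compare it with the RP / PSG" studies done at the Sleep Unit. The Rationale gives the purpose of the screening model as "detecting and classifying patients with OSA according to severity", and the Limitations section describes the main aim as separating severe from mild disease. A further objective judges the CPAP decision that the primary care physician makes with the AMS.

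The data are paired. Under Design and Validation Time, "All patients eligible for inclusion in the study will perform the two models of validation", and for RP/PSG the protocol adds that "in every case, an overnight sleep study will be done in the Sleep Unit". Outcome Measures lists "Primary outcome: apnea-hypopnea index (AHI) obtained in Sleep Unit by PSG/RP study", and lists an AHI among the AMS variables too.

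The section Data management and analysis opens with "The main objective of this study is to obtain a sufficiently accurate calculation of the area under the curve (AUC") of the ROC curve. It then names:
- descriptive statistics;
- chi-square or Fisher tests for qualitative variables;
- for quantitative variables, "In the case of quantitative variables, the T-test or Mann-Whitney U test will be performed according to normal distribution";
- logistic regression, with a Hosmer-Lemeshow test to validate the model and the AUC to calibrate it.

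No analysis of the difference between the two AHI readings within a patient is named.

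**The concern.** Comparing a device with a reference raises two questions. One is whether the device ranks patients correctly, so that some cut-off separates those with OSA from those without. The other is whether its number equals the reference number, so that a reading can be taken as it stands. The AUC answers only the first. Severity classes are absolute AHI ranges; the only levels in the protocol, in the Background, are above 15 and above 30. If the AMS AHI is read on that scale in Primary Care, the second question matters.

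At stake is the conclusion that the AMS is valid for severity. A high AUC could be reported as validity while patients are systematically placed in too low or too high a class. The plan also assigns calibration to the AUC, which carries no information about scale.

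**Working it through.** **Inputs from the protocol.** Sample size 198, 15% losses, minimum prevalence 25% (Sample size); AHI levels 15 and 30 (Background). Evaluable patients: 198 × 0.85 = 168.3, so 168, of whom 168 × 0.25 = 42 have OSA.

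**Precision of the AUC.** The plan expects it to be within 10 points. The Hanley-McNeil formula with 42 cases and 126 non-cases gives a 95% half-width of 0.065 at an AUC of 0.90 and 0.086 at 0.80. The plan's expectation is met. The issue is what the AUC measures, not how precisely.

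**Invariance (no assumption needed).** AUC = P(AMS of a case > AMS of a non-case). For any constant k > 0, kX₁ > kX₂ exactly when X₁ > X₂, so the AUC is the same for every k. The logistic model is no more informative: with predictor kX, the coefficient β/k gives identical fitted probabilities, so the Hosmer-Lemeshow result is also unchanged.

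**Size (assumptions not in the protocol).** Log-normal AHI with log-SD 1.1 for both methods; 25% of reference AHI above 15; correlation ρ of the log values. The AMS reads k times the true scale.
- Standardised reference threshold at 15: a = 0.674.
- Standardised AMS threshold: b = a − ln(k)/1.1. For k = 0.7, b = 0.674 + 0.357/1.1 = 0.999.
- Sensitivity = P(Z₁ > a, Z₂ > b) / P(Z₁ > a), with Z₁ and Z₂ bivariate normal with correlation ρ.
- At ρ = 0.8: 0.1691/0.25 = 0.68 for k = 1, and 0.1242/0.25 = 0.50 for k = 0.7.

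| ρ | AUC for AHI >15, any k | Sensitivity at 15, k = 1 | Sensitivity at 15, k = 0.7 |
|---|---|---|---|
| 0.5 | 0.74 | 0.48 | 0.34 |
| 0.7 | 0.84 | 0.60 | 0.44 |
| 0.8 | 0.89 (0.895) | 0.68 | 0.50 |
| 0.9 | 0.95 | 0.77 | 0.57 |

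At ρ = 0.8, sensitivity at 30 falls from 0.56 to 0.37. Among 42 patients above 15, about 28 are read as above 15 by the unbiased device (42 × 0.676) and about 21 by the device reading 30% low (42 × 0.497).

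**Second set of assumptions.** Log-SD 1.0, and random AMS error with log-SD 0.3. The AUC is 0.977 at every k. Sensitivity at 15 falls from 0.868 (k = 1) to 0.623 (k = 0.7). At k = 1.5 the error goes the other way: specificity falls from 0.944 to 0.797.

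**Where scale does not matter.** Under this second set, if the cut-off is chosen from the data for 90% sensitivity, specificity is 0.926 at every k. Only the cut-off moves: 14.0 at k = 1, 9.8 at k = 0.7, 21.0 at k = 1.5.

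**What 168 pairs can show.** The 95% half-width for the mean difference is 1.96/√168 = 0.15 SD of the differences. For each limit of agreement it is 1.96 × √(1/168 + 1.96²/(2 × 167)) = 0.26 SD. At ρ = 0.8 the SD of the log differences is 1.1 × √(2 × 0.2) = 0.696, so the mean is known to ±0.105. A 30% under-reading is ln 0.7 = −0.357 and would be plain.

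**The case against.** The best defence is that the objective speaks of identifying patients, which is discrimination, and that the Hypothesis concerns a model combining clinical variables with device data. Such a model absorbs a constant scale error in its coefficient or cut-off. This stands: for detection, the AUC is a proper measure. It does not cover severity classification or a direct reading of the AMS AHI.

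A second defence is that a statistical analysis plan, not shown, may name an agreement statistic. That is possible. But the protocol itself sets out the methods, makes the AUC the main aim and gives it the calibration role, so the point concerns what is stated.

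Several stronger readings are tempting and are not supported:
- **That the plan tests AMS against RP/PSG with unpaired tests.** A reader might infer this because Mann-Whitney U is for independent groups. But the sentence belongs to the bivariate analysis that feeds the logistic regression, where patients with and without OSA are independent groups. The plan never assigns it to the paired readings, so the power of an unpaired test there is not a measure of this plan.
- **That nothing planned could reveal a bias.** Descriptive summaries of both AHIs, the false-positive and false-negative counts in the cost analysis, and the comparison of CPAP decisions could each hint at one. They are indirect, and no AMS cut-off or agreement statistic is fixed for them.
- **That the AMS is known to read low.** The AMS is scored over questionnaire-defined recording time, while the Background defines AHI per hour of sleep. But RP has no EEG either, and the Limitations section says its values can be underestimated. Neither the direction nor the size of any AMS error is established.
- **That 15 and 30 are the plan's AMS cut-offs.** They appear only as background on cardiovascular risk.

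**Conclusion.** The point holds in limited form. The AUC can support a claim that the AMS detects OSA at a suitably chosen cut-off. It cannot support a claim that the AMS AHI agrees with the RP/PSG AHI or can be read as it stands for severity, although the protocol sets out to compare the device with RP/PSG and to classify severity.

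The invariance of the AUC is exact. The size is illustrative: a 30% under-reading costs 14 to 21 percentage points of sensitivity at AHI >15 across correlations of 0.5 to 0.9 (0.48 to 0.34; 0.77 to 0.57), and 18 points at 0.8, with no change in the AUC. These figures assume log-normal AHI and tie the protocol's 25% to AHI >15, which the protocol does not do. They also ignore the heavier testing of patients with a high Berlin score. Even the unbiased device misses 32% at a correlation of 0.8, so only the drop between columns is due to bias. This is a worthwhile, inexpensive improvement, not a flaw that invalidates the AUC analysis.

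**What to change.** In Data management and analysis, add a within-patient comparison of the AMS with RP/PSG:
- the mean AHI difference with 95% CI and Bland-Altman limits of agreement, on the log scale if the data are skewed;
- paired cross-tables of AMS AHI against RP/PSG AHI at 15 and 30, used only as analysis levels because the protocol cites them, with sensitivity and specificity of the AMS reading as it stands and their 95% CIs.

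State that the validity conclusion for severity rests on these alongside the AUC, and that the t-test, Mann-Whitney, chi-square and Fisher tests apply to the comparison of predictors between patients with and without OSA.

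The cost is a few sentences and slightly more analysis. Both AHIs are already collected and no further patients are needed. The AMS may look less favourable than its AUC suggests.

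### Bivariate significance plus an uncapped set of clinically relevant variables is a poor entry rule for a prediction model with about 42 to 77 OSA cases and 27 to 28 possible predictors

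*Protocol*

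**What the plan says.** The Protocol, Data management and analysis, plans logistic regression to find the best clinical prediction model. Its entry rule is: "Variables showing clinical significance in the bivariate analysis and those considered clinically relevant will be included". The Methods paragraph of the project summary repeats it.

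The bivariate tests are named just before the rule: chi-square or Fisher for qualitative variables, t-test or Mann-Whitney for quantitative ones. The level is given as "In all cases, the significance level will be, as usual, 5" per cent, two-sided. No maximum number of predictors is stated. The resulting model is to be validated by the Hosmer-Lemeshow test and calibrated by the AUC.

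The variables to be collected are under Outcome Measures. For the ambulatory monitoring study (AMS) they are "AHI, mean saturation, 4% desaturation index (ID4%), 3% desaturation index (ID3%) and CT90" (the last as a percentage). Clinical, questionnaire and spirometry items come on top.

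The Sample size section rests on sensitivity, not on model building: "a total sample of 198 patients was estimated as necessary to achieve a sensitivity of 90" per cent, "considering a minimum prevalence of 25% of OSA in the population attending Primary Care Medicine". The sleep studies are then done in "all patients with a high probability of OSA but in only 1 of 3 patients with a low probability".

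**The concern.** Screening many variables on the data that also fit the model has three known effects. Noise variables enter by chance, real predictors drop out by chance, and the coefficients that survive are too large. Variables forced in as clinically relevant, without limit, add further parameters. The fewer the cases per candidate, the stronger these effects.

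The model is the study's main product. The Rationale expects Primary Care physicians to use it to rule out OSA and to prioritise severe disease. An overfitted model gives new patients probabilities that lie too near 0 or 1, and it looks better in the development data than it will in use. The planned checks would not show this. A Hosmer-Lemeshow test on the development data assesses fit to the same patients, and the AUC measures discrimination, not calibration.

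**Working it through.** **1. The plan's own sample size.** Inputs from Sample size: sensitivity 90%, minimum prevalence 25%, and "Assuming 15% of losses to follow-up, an error of 5% and a power of 90" per cent. The null sensitivity is not stated; 70% is assumed here.

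- Cases: n = ((1.96·√(0.7·0.3) + 1.2816·√(0.9·0.1)) / 0.2)² = 41.1, so 42.
- 42 / 0.25 = 168 evaluable patients.
- 168 / (1 − 0.15) = 197.6, so 198. This matches.

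Forwards, without the assumed null: 198 × 0.85 = 168.3 evaluable, and × 0.25 = 42.1 cases.

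**2. Effect of Berlin enrichment.** With 396 questionnaires and 198 studied, H + L = 396 and H + L/3 = 198 give H = 99 high-probability and L = 297 low-probability patients. If 25% of all 396 have OSA, there are 99 cases. With x of them in the high group, evaluable cases are 0.85 × (x + (99 − x)/3).

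- x = 25 (Berlin uninformative): 0.85 × 49.7 = 42.2.
- x = 86 (assumed upper end): 0.85 × 90.3 = 76.8.

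**3. Possible predictors under Outcome Measures.** Anthropometric and demographic 6; risk factors and heart disease 9; cerebrovascular disease, peripheral vascular disease and drug treatment 3; symptom questionnaire, Berlin, spirometry and Epworth 4 (each counted once); AMS 5. The total is 6 + 9 + 3 + 4 + 5 = 27, or 28 if cerebrovascular disease is split once. Weight, height, BMI and waist overlap, as do ID3%, ID4% and the device AHI.

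**4. Cases per candidate.** 42/28 = 1.5 and 76.8/28 = 2.7. At 10 cases per parameter, 42 cases support 42/10 ≈ 4 parameters. Five parameters would have 42/5 = 8.4 each.

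**5. Expected shrinkage.** The size formula for a uniform shrinkage S is N = P / ((S − 1)·ln(1 − R²/S)), with R² the Cox-Snell value. At 25% prevalence and assumed Nagelkerke R² of 0.15, 0.3 or 0.5:

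- P = 28, S = 0.9: N = 2345, 1098 or 595, against about 168 planned.
- P = 28, N = 168: S = 0.41, 0.60 or 0.73.
- P = 10, S = 0.9: N = 838, 392 or 213. N is proportional to P, so P = 5 needs half: about 419, 196 or 107. A short list of five therefore still needs shrinkage unless the predictors are strong.

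**6. Simulations** (168 patients, 25% cases, entry at p < 0.05, performance in new patients; all settings assumed). Cells show AUC / calibration slope.

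| Setting | Best AUC | Screened | Fixed five |
|---|---|---|---|
| 28 candidates, correlated AMS and adiposity blocks; list holds all real predictors | 0.79 | 0.74 / 0.64 | 0.78 / 0.83 |
| Same, stronger | 0.88 | 0.84 / 0.78 | 0.87 / 0.90 |
| Same, strongest | 0.93 | 0.91 / 0.78 | 0.92 / 0.88 |
| 27 independent candidates; list misses one of three real predictors | 0.77 | 0.732 / 0.70 | 0.715 / 0.78 |
| Same, stronger | 0.83 | 0.796 / 0.79 | 0.788 / 0.85 |

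A further set with correlated blocks, 25% or 40% cases and best AUC 0.75 to 0.90 gave screened models an AUC 0.02 to 0.06 below the best and slopes of 0.61 to 0.81. A fixed five-variable list that missed one weaker real predictor lost at most 0.03 (slope 0.83 to 0.91). Ridge on the fixed list brought the slope to about 1.0.

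Harsher settings exist. With six modest real predictors among 28 candidates and a common correlation of 0, 0.2 or 0.4, the apparent AUC was 0.79, 0.85 or 0.91 against 0.70, 0.76 or 0.77 in new patients, with slopes of 0.62, 0.59 and 0.41. That optimism of about 0.09 to 0.13 is of the order of the 10% AUC accuracy that the protocol sets itself.

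**The case against.** **The case count is a floor.** The 25% is called a minimum, and the sampling favours high-probability patients. This stands, so a single figure of 42 would be misleading. The count also depends on the AHI cut-off that defines OSA in the model, which the protocol does not fix. At the assumed upper end, however, there are still fewer than 3 cases per candidate with 28 candidates.

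**The candidate count is a reading.** The variables are listed as secondary outcomes, and the rule speaks of clinical, not statistical, significance, so part of the entry is by judgement. This stands in part. But the paragraph names hypothesis tests and a 5% level and gives no shorter list. The objectives say that the model rests on clinical variables and monitoring data, which are these items.

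**A dominant device index may protect the model.** The AMS measures the same construct as the reference test. The cited Primary Care model reported sensitivity 0.88 and specificity 0.82, an AUC of about 0.93 under an equal-variance binormal assumption. With a best AUC of 0.93 and independent candidates, screening alone gave 0.913 against 0.924 for a fixed list, with equal slopes (0.875 and 0.872). With six forced variables, an assumed number, it gave 0.904 and a slope of 0.77. So the AUC loss can be as small as 0.01 to 0.02, and the calibration loss can vanish in the most favourable setting. With correlated blocks at the same AUC, the screened slope was still 0.78.

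**A short list is not free.** A reader might infer that a fixed list always discriminates better. It does not: in the last two table rows, a list that misses one real predictor has a lower AUC than screening, although its slope is better.

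**The SAP is not shown.** It may add shrinkage or bootstrap validation, so their absence is no finding. The entry rule itself is in the protocol.

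**Conclusion.** The point holds as a criticism of a stated method. Under the protocol's own planning figures there are about 1.5 cases per candidate, and about 2.7 at the assumed upper end of enrichment. The expected consequence is a calibration slope of about 0.6 to 0.8 in new patients and an AUC about 0.01 to 0.06 below the best achievable. Some assumed settings fall outside these ranges in both directions, with slopes of 0.41 and 0.875. The direction is firmer than the size.

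Three stronger readings are tempting and not supported. The documents do not show that the model will certainly be overfitted or unusable, since that depends on how strongly the AMS indices predict and on how many variables are forced in. They do not make 42 the expected number of cases. And nothing in them says that continuous predictors will be categorised, so that is no part of this point.

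This is a worthwhile, low-cost improvement to the analysis, not a defect in the design.

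**What to change.** In Data management and analysis, and in the matching sentence of the project summary:

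- Remove bivariate significance as an entry rule.
- Before data lock, fix a short predictor list on clinical grounds and prior literature: about 4 to 5 parameters at 42 cases. One example is one AMS index, one adiposity measure, age, sex and the Berlin result; the exact choice is the sponsor's.
- Fit the list with shrinkage, either ridge regression or a bootstrap-estimated slope.
- Keep the bivariate tables as description, and label any wider search for predictors exploratory.

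This changes analysis wording only; no patient, visit or measurement is added. The downside is that a useful predictor outside the list would be found only in the exploratory analysis. If the list misses an important predictor, the AUC gain over screening shrinks or may reverse, while calibration is still generally better.
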